Participants randomized into the watchful waiting group will receive standardized oral information and written instructions which, like those described by Fitzgibbons et al., will deal with physical activity, diet, pain and pain medication, constipation management, sexual activity, hernia warning signs, and symptoms of acute incarceration [24]. They will be told to consult a physician immediately if acute symptoms develop. Physical examinations will be performed during follow-up visits at 1 month, 12 months and 24 months by a physician. After 6 and 18 months, participants will also be interviewed regarding potential hernia-related pain or discomfort by a physician or a study nurse. The frequency and scope of study visits is presented in table 1.

**Table 1 T1:** Frequency and scope of study visits

Visit	Visit 1 (Screening)	Visit 2 (Day of surgery)	Visit 3 (1 month post OP)	Visit 4 (6 months post OP)	Visit 5 (12 months post OP)	Visit 6 (18 months post OP)	Visit 7 (24 months post OP)
Demographics and baseline clinical data	X						

Inclusion/exclusion criteria	X						

Randomization	X						

Clinical examination	X		X		X		X

Ultrasound	X						X

Pain level (SPS, PDI)	X			X	X	X	X

Quality of life (SF-36)	X			X	X	X	X

Mental health (HADS-D)	X						X

Patient satisfaction (Likert scale)	X			X	X	X	X

Surgical intervention		X					

Postoperative complications			X		X		X

AEs/SAEs		X	X	X	X	X	X

Costs of treatment		X	X	X	X	X	X

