Postoperative bleeding is defined as a bleeding requiring either blood transfusion or reoperation. Pneumonia is defined as an infection of the lung that can be caused by nearly any class of organism (bacteria, amoebae, viruses, fungi, and parasites) known to cause human infections. A urinary tract infection is an infection of one or more structures in the urinary system. A deep vein thrombosis is a blood clot in a major vein that usually develops in the legs or pelvis. Pulmonary embolism is an obstruction of a blood vessel in the lungs, usually due to a blood clot. A bowel obstruction is defined as the necessity to insert a nasogastric tube longer than 72 h after the operation or the necessity to reoperate. A recurrent hernia is a hernia diagnosed by physical examination or ultrasound after surgical hernia repair.

Other AEs are: vomiting and pain at rest. The following severe adverse events (SAEs) are monitored: reoperation, rehospitalization, ICU admission, acute incarceration, death. The principal investigator is informed about SAEs within 3 days.

An independent Data Safety Monitoring Board (DSMB) consisting of 3 external experts (2 clinical experts and 1 statistician) will meet annually to address patient safety and perform risk-benefit assessments. In accordance with its standard operating procedures (SOPs), the DSMB reviews the accumulating data from the ongoing trial to ensure continued patient safety. The DSMB assesses study aspects such as progress, integrity, and design and makes recommendations to the coordinating investigator regarding modification, continuation or termination of the study.

The primary statistical analyses will be conducted by the Institute of Biometry and Epidemiology at the Charité using an intention-to-treat (ITT) approach. Interim analysis is not planned. Additional as-treated analyses will be performed. Investigators are masked to the patient's treatment arm at the time of enrolment. The statistician will be blinded while performing data analyses.

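### Several safety terms and the Table 1 time axis presuppose an operation, so events are defined and observed unequally in the two arms

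*Protocol article*

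**What the plan says.** All references are to the Protocol article.

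- **Serious events** (Monitoring and statistical analysis): "The following severe adverse events (SAEs) are monitored: reoperation, rehospitalization, ICU admission, acute incarceration, death".
- **Bowel obstruction** (same section): "A bowel obstruction is defined as the necessity to insert a nasogastric tube longer than 72 h after the operation or the necessity to reoperate". The objectives section lists bowel obstruction among the postoperative complications.
- **Schedule** (Implementation of the study, Table 1): there is one schedule for both arms. Randomisation is at Visit 1. The next column is the operation (the heading reads "Visit 2 (Day of surgery"), and Visits 3 to 7 are labelled in months after the operation. The AE/SAE row has no mark at Visit 1 and a mark at every visit from Visit 2 on.
- **Watchful-waiting follow-up** (Implementation of the study): "Physical examinations will be performed during follow-up visits at 1 month, 12 months and 24 months by a physician" and "After 6 and 18 months, participants will also be interviewed regarding potential hernia-related pain or discomfort by a physician or a study nurse". Neither sentence says what the months are counted from.
- **Primary endpoint** (Objectives, endpoints and sample size calculation): assessed two years from enrolment, not from surgery.
- **Use of the safety data** (Monitoring and statistical analysis): a DSMB meets once a year for risk-benefit assessment, and the primary statistical analyses follow intention to treat.

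**The concern.** In a trial of operating against not operating, a safety term must be able to apply to a patient in either arm, and the clock must start at the same moment in both. Several printed terms fail the first condition and Table 1 fails the second.

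At stake are the events that decide whether waiting is acceptable short of an emergency: an unplanned admission because of the hernia, a repair that was not planned, or an obstruction that settles without meeting the description of acute incarceration. If some sites record these and others do not because the term does not fit, the counts differ between arms and between sites for reasons unrelated to treatment. In the repair arm, an event while waiting for the operation belongs to that arm under intention to treat, but it has no marked visit of its own.

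**Working it through.** The plan prints no figure on this point, so the check is a comparison of wording and schedule.

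**1. Terms, applied to a watchful-waiting patient who has had no trial operation**

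| Printed term | Can it be met literally? |
|---|---|
| Reoperation (SAE) | No: a first hernia repair is not a repeat |
| Rehospitalization (SAE) | No: a first admission is not a repeat |
| ICU admission (SAE) | Yes |
| Acute incarceration (SAE) | Yes |
| Death (SAE) | Yes |
| Bowel obstruction (AE) | No: both limbs, "necessity to insert a nasogastric tube longer than 72 h after the operation or the necessity to reoperate", need an earlier operation |
| Sepsis, pneumonia, urinary tract infection, deep vein thrombosis, pulmonary embolism (AE) | Yes |
| Vomiting, pain at rest (AE) | Yes |

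So 2 of 5 SAE terms, and the only obstruction term, presuppose an operation or admission. Postoperative bleeding ("Postoperative bleeding is defined as a bleeding requiring either blood transfusion or reoperation") and recurrent hernia are also tied to surgery, but rightly so: they are harms of the repair and have no counterpart in an unoperated patient.

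A first admission, first unplanned repair or obstruction in this patient is therefore captured as a serious event only if acute incarceration, ICU admission or death comes with it.

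**2. Schedule**

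Table 1 has 7 visits and marks AEs/SAEs at 6 of them (Visits 2 to 7). The first mark is on the day of surgery.

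- Repair arm: the interval from randomisation (Visit 1) to operation (Visit 2) lies before the first mark.
- Watchful-waiting arm: there is no day of surgery, so Visit 2 has no counterpart and the origin of the visit months is unstated.

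**3. Two clocks**

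Let w be the weeks from randomisation to operation. The article does not give w, so the values below are assumptions. If visits run from the operation, the repair arm's marked window is weeks w to 104 + w after randomisation. If the watchful-waiting months run from randomisation, that arm's window is weeks 0 to 104. The share of the first two years after randomisation that precedes the repair arm's first mark is w/104:

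- w = 2: 2/104 = 1.9%
- w = 4: 4/104 = 3.8%
- w = 8: 8/104 = 7.7%
- w = 12: 12/104 = 11.5%

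The last repair-arm visit, at which the primary endpoint would be taken, likewise falls w weeks later than two years from enrolment.

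**4. Direction**

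Events lost under step 1 fall in the watchful-waiting arm and flatter waiting. Events lost under step 2 fall in the repair arm and flatter surgery. Nothing in the article says which is larger.

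**The case against.** A reader might infer that the harms of watchful waiting go uncounted, or are zero by definition. The article does not support that.

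- The SAE sentence itself names acute incarceration, ICU admission and death, none of which needs a prior operation. Acute incarceration is the harm the Background treats as the main risk of waiting.
- The objectives section makes incarceration frequency and hernia size named outcomes in the watchful-waiting group and records mortality.
- Table 1 marks AEs/SAEs at months 1, 6, 12, 18 and 24, when watchful-waiting patients are also examined or interviewed.
- Inpatient costs, including operations, are to be collected for each participant, and the planned as-treated analyses need crossover repairs to be recorded. Admissions and first repairs would therefore enter the database, though not necessarily as safety events.

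All of this stands, and it limits the point to particular events.

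Three further arguments stand in part. First, a mark at Visit 2 may be meant to cover everything since Visit 1, and the 1-month visit could cover the start of follow-up in watchful waiting. That is possible, but the table does not say so. Second, every participant has had earlier abdominal surgery, so reoperation and rehospitalization might be read loosely. On that reading, however, the allocated repair would itself be a reoperation and hence a serious event, which can hardly be meant. The terms are at best ambiguous, and ambiguity across the 19 listed sites does not give comparable counts. Third, the full protocol and the completed eCRFs are not shown and may settle the wording. The point is therefore about rules the article prints, not proof that events were not collected.

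**Conclusion.** The point holds in a limited form. Taken literally, the printed rules give the two arms different event definitions and different observation windows. The affected events are a first unplanned admission, a first unplanned repair and an obstruction without trial surgery in watchful waiting, together with any event between randomisation and operation in the repair arm.

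The effect on the safety comparison and the DSMB review could go either way, and its size is unknown. It might be tempting to attach a number. For example, 5% of the 318 patients per arm (636/2) would be about 16 lost events (318 × 0.05 = 15.9). But the article gives no rate for such events, so that figure only restates its own assumption. It also supposes that none of the events is caught by another listed term and that all losses fall in one arm, which step 4 of the check contradicts.

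The conclusion assumes that sites apply the terms as printed and that the full protocol and eCRF do not redefine them. The definition of the primary pain endpoint is not affected, but the visit at which it is measured needs the same reconciliation of time origin.

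**What to change.** - State that AEs and SAEs are counted from randomisation in both arms, and start the AE/SAE row of Table 1 there.
- Replace rehospitalization with any unplanned hospital admission, flagging those related to the hernia or its repair.
- Replace reoperation with any hernia-related operation other than the allocated index repair. Include a first repair in a watchful-waiting patient, and flag each operation as elective or emergency.
- Define bowel obstruction without reference to a prior operation. The existing definition can remain for the postoperative complication outcome.
- Reconcile the operation-based visit labels in Table 1 with the enrolment-based timing of the primary endpoint, and name time zero for the watchful-waiting arm.

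The cost is revised wording, changes to eCRFs that the article says are already completed, and slightly more SAE reports. No visits or staff are added, and treatment in either arm is unchanged.

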## Discussion

This article describes the design of a trial comparing surgical and nonsurgical management of incisional hernias. Incisional hernia repair is not a low-risk operation, and it is associated with a high recurrence rate and a high percentage of postoperative pain. Treatment of incisional hernias represents a large surgical and socioeconomic problem. Up to now, surgical treatment has been recommended for incisional hernia patients regardless of whether there are any symptoms indicating a high risk of acute incarceration with serious complications. No studies have as yet defined the exact indications for incisional hernia repair or described the natural course of an incisional hernia, including the risk of acute incarceration. Randomized controlled trials performed in the past few years have shown that watchful waiting is a reasonable option for mildly symptomatic inguinal hernias.

To our knowledge, this is the first study to compare watchful waiting with surgical repair of oligosymptomatic incisional hernias in a prospective randomized setting. The study will provide very useful information regarding the natural course of incisional hernias and the rate of incarceration. We hypothesize that pain intensity during everyday activities does not differ between the compared groups and that the incarceration rate is low. If this should be confirmed, it would be justifiable to apply a watchful waiting strategy for oligosymptomatic incisional hernias and to thus avoid the risks and costs of surgery.

### Trial status

AWARE is funded by the German Research Foundation (DFG; project funding reference number LA 2380/3-1). Thus adequate financial resources are available to hire appropriate personnel (e.g., research nurses, project managers, monitors, and data managers) and cover additional expenses.

The study protocol has been approved by the Ethics Committee of the Charité. The trial protocol was registered http://clinicaltrials.gov/ on May 05, 2011 and was given a unique number for a worldwide identification of this trial (identifier: NCT01349400).

All 19 study sites received a study synopsis and signed the Declaration of Commitment. Participating study sites are: Charité Campus Benjamin Franklin, Berlin; Charité Campus Mitte, Berlin; Charité Campus Virchow Klinikum, Berlin; Universitätsklinikum Heidelberg; Universitätsklinikum Freiburg; Universitätsklinikum Carl Gustav Carus Dresden; Medizinische Fakultät Mannheim; HELIOS Klinikum Erfurt; HELIOS Klinikum Schwerin; Klinikum Südstadt Rostock; Johannes Gutenberg Universität Mainz; Klinikum Augsburg; Universitätsklinikum Bonn; Krankenhaus Sinsheim; Universitätsklinikum Münster, Diakoniekrankenhaus Henriettenstiftung Hannover, Ludwig-Maximilians-Universität München, Unfallkrankenhaus Berlin, Klinikum rechts der Isar der Technischen Universität München.

This declaration specified the inclusion and exclusion criteria, and the trial sites used hospital data management systems to estimate the annual number of patients willing to participate. According to these declarations, 949 patients will be enrolled in 36 months. Each center plans to enroll 5 to 40 patients each year. Non-university and university medical centers are involved to increase the generalizability of the study. All participating centers are familiar with clinical studies. Eight of them belong to the Chir-Net Germany, a network of regional surgical centers funded by the Federal Ministry of Education and Research (BMBF) and devoted to the development and implementation of multicenter clinical trials. All study centers have received the final study protocol. In 10 centers, the approval of the local ethics committees has been obtained.

The electronic case report forms (eCRFs) and the randomization tool have been completed.

An initiation meeting in Berlin took place in January 9, 2012 to introduce the principal investigators and to familiarize the study centers with the details of screening, randomization, surgery, monitoring and follow-up. The whole study team was present. The first patient was randomized at Charité Campus Benjamin Franklin November 14, 2011.

The recruitment period is planned for 36 months (until October 2014); last-patient-out should be achieved in November 2016.

## Abbreviations

AE: Adverse Event; ASA: American Society of Anesthesiologists; AWARE: Watchful Waiting vs. Repair of Oligosymptomatic Incisional Hernias; BMBF: Bundesministerium für Bildung und Forschung (Federal Ministry of Education and Research); bpm: Beats per minute; CI: Confidence interval; CONSORT: Consolidated Standards of Reporting Trials; DFG: Deutsche Forschungsgemeinschaft (German Research Foundation); DSMB: Data Safety Monitoring Board; eCRF: Electronic Case Report Form; HADS-D: Hospital Anxiety and Depression Scale - Deutsche Version (German version); ICU: Intensive Care Unit; IMC: Intermediate Care Unit; InEK: Institut für das Entgeltsystem im Krankenhaus (Institute for Hospital Reimbursement System); IPOM: Intraperitoneal onlay mesh; ITT: Intention-to-treat; KKS: Koordinierungszentrum für Klinische Studien (Coordinating Center for Clinical Studies); OP: Operation; PDI: Pain Disability Index; SAE: Serious Adverse Event; SD: Standard deviation; SF-36: Short Form 36 Health Survey Questionnaire; SOP: Standard operating procedure; SPS: Surgical Pain Scales.
